## Research Protocol: Creating Healthier Communities – AAMWI & OSU

|    |                                                                                                                                                 |                                                    |                                                           |
|----|-------------------------------------------------------------------------------------------------------------------------------------------------|----------------------------------------------------|-----------------------------------------------------------|
| 21 | 
 
• Introduction to Global One Health Initiative (30 min)
 
• Physical Activity (45 min)
 
 | Global One Health Initiative                       | Weight, BP check                                          |
| 22 | 
 
• DPP Session 16: Ways to Stay Motivated (30 min)
 
• Physical Activity (45 min)
 
       |                                                    | Weight Check                                              |
| 23 | 
 
• The importance of 7-8 hours of sleep (30 min)
 
• Physical Activity (45 min)
 
         |                                                    | Weight Check                                              |
| 24 | 
 
• Introduction to ResearchMatch (30 minutes)
 
• Physical Activity 45 min
 
              | OSU Center for Clinical and Translational Sciences | Complete Surveys online via redcap Labs and Vitals |

| Table 2. Project Timeline and Outcomes |        |    |    |    |        |    |    |    |
|----------------------------------------|--------|----|----|----|--------|----|----|----|
|                                        | Year 1 |    |    |    | Year 2 |    |    |    |
| Milestone                              | Q1     | Q2 | Q3 | Q4 | Q1     | Q2 | Q3 | Q4 |
| IRB approval                           | •      |    |    |    |        |    |    |    |
| Recruitment/enrollment                 | •      | •  |    |    |        |    |    |    |
| CHW training                           | •      | •  |    |    |        |    |    |    |
| Intervention                           |        |    | •  | •  |        |    |    |    |
| Data analyses                          |        |    |    |    | •      | •  |    |    |
| Dissemination/manuscripts              |        |    |    |    |        |    | •  | •  |

Figure 3. Study Timeline

### **Data Measurements:**

The Reach, Efficacy, Adoption, Implementation, and Maintenance (RE-AIM) framework will guide evaluation of the intervention. Effectiveness and maintenance: Life's Simple 7 measures (secondary outcomes) and HRQOL, Perceived Stress, Sleep Quality, Depressive Symptoms collected pre-mid-post-intervention. Adoption (acceptability): The participants will be asked to complete a survey of program satisfaction, including the content, length, and dose of the intervention. Implementation (treatment fidelity): We will follow the NIH's Behavioral Change Consortium treatment fidelity guidelines in study design, study staff training, treatment delivery, treatment receipt, and treatment enactment, to ensure treatment fidelity in the intervention.

Data from participants will include self-report measures and survey data will be collected via paper or directly entered into Redcap. Biometric measurement will include blood pressure, cholesterol, glucose, and body mass which will be entered into Research Electronic Data Capture (REDCap) by health coaches. Data will be coded. After completion of data collection, the PI will retain the master list and subjects will be de-identified in data analyses and publications. Measure descriptions are included below:

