### **Research Structure:**

In this single-arm pilot program, we will enroll 100 AA male participants from the annual AAMWI walk/health fair who have poor or average cardiovascular health ( $< 4$  LS7 metrics in the ideal range) with the goal of accomplishing aims exhibited in Figure 2. Our intervention involves two components: a community health worker (CHW) and peer team. Each participant will be assigned to a CHW and grouped into a team of 10 participants based on participant proximity to a central meeting location (total 10 teams). The CHW will assist in activating individual participants to engage in primary care, social support services, and enrollment in ResearchMatch. Within the teams, health coaches will assist the study team in implementing the community-based lifestyle intervention spanning LS7 principles and ResearchMatch, as shown in Figure 2 below.

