### Intervention:

The intervention is a 24-week community-based lifestyle intervention to improve cardiovascular health among AA males involving two components: a CHW and peer team. Each participant will be assigned to a CHW and grouped into a team of 10 participants based on participant proximity to a central meeting location (i.e. Columbus Recreation and Parks centers and YMCAs). Each team's four health coaches will deliver content and coaching around the lifestyle intervention described below. The intervention will be applied evenly to all participants. Health coaches will implement the curriculum [Table 1] utilizing resources from the partnering organizations. Health coaches will meet with participant teams weekly for 75 minutes. Key health coach activities include delivering education, establishing and monitoring progress in achieving individual and team-based SMART (specific, measurable, achievable, relevant, and time-bound) wellness goals.

| Weeks | Session topics                                                                                                                                                                                                                                                                                                                                                                                                                                                                                                                                                                                                                                                                                                       | Partners                   | Study Measurements                                                                       |

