#### **Confidentiality**

Demographic, screening and survey data will be stored electronically behind the OSUWMC firewall in REDCap. Only the PI, co-investigators and the research assistants working on the project will have access to the data. All computers that will be used to store data will be password protected behind the OSUWMC. Electronic copies of forms will be stored on a secure dedicated server with appropriate firewalls. The system will use 128-bit encryption (SSL certificate) to transfer data between the machines. This technology is the same as that used for online e-commerce applications to protect consumer information such as name, address, and credit card details. Servers are scanned for viruses and systems are in-place to detect attempts at unauthorized entry. The data base server is backed up 3 times a day internally. Personal information will be stored confidentially for the minimum required amount of time after study completion.

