### **Monitoring the Safety of Individual Participants**

A. A research team member will be present during all testing procedures to monitor the safety of the individuals. A study team member will review any adverse events that may occur after or between visits. The primary investigator and co-investigators will monitor study progress on a weekly basis. Regular check-ins by the Principal Investigator

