## **Research Protocol: Creating Healthier Communities – AAMWI & OSU**

### **E. Plan for assuring data accuracy and protocol compliance:**

The clinical research coordinator and/or investigator will be responsible for collecting and recording all relevant data for the protocol. As these results are collected and adverse events will be identified and reported to the principal investigator. Adverse events will be reported as described above. The principal investigator will determine the relationship of the event(s) to the intervention(s), procedure(s), and/or agent(s) of the protocol and decide the appropriate course of action for the study participant(s). Standard operating procedures for data collection and for conducting procedures will be developed. Data will be randomly audited (10% of subjects) by the study PI on an ongoing basis. Study staff will complete readily available training modules on the use of the REDCap database.

Nothing in the DSMP replaces an investigator's or study coordinator's responsibility for prompt and appropriate reporting of serious adverse events, protocol amendments, data collection procedures, etc. to the OSU ORRPIRB, sponsor(s), or other responsible parties. Any reporting required by the DSMP is in addition to these core compliance responsibilities.

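### The coaches who deliver the intervention also enter its biometric outcomes, which conflicts with the protocol's own statements on who records data and who has access

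*Protocol*

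**What the plan says.** In the Data Measurements section the biometric values (blood pressure, cholesterol, glucose and body mass) are to be "entered into Research Electronic Data Capture (REDCap) by health coaches".

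The Intervention section describes what those coaches do. Each team's "four health coaches will deliver content and coaching around the lifestyle intervention described below", and their key activities include "establishing and monitoring progress in achieving individual and team-based SMART" wellness goals. The Research Structure section says that "health coaches will assist the study team in implementing the community-based lifestyle intervention", which describes them as helpers of the study team. The Instructors section identifies them as student volunteers.

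Other sections place the data task elsewhere. Section E, on data accuracy and protocol compliance, states: "The clinical research coordinator and/or investigator will be responsible for collecting and recording all relevant data for the protocol". The Data Management section gives collection to study staff in one sentence and to study team members in another. The Confidentiality section says: "Only the PI, co-investigators and the research assistants working on the project will have access to the data". Coaches are not on that list.

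On attendance, the section on monitoring individual participants' safety says: "A research team member will be present during all testing procedures to monitor the safety of the individuals".

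**The concern.** There are two problems, and the second makes the first worth more than a wording edit.

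First, the protocol gives incompatible answers to who records the outcome data and who may see them. Staff following Data Measurements would give coaches an entry role that Confidentiality, read literally, does not allow.

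Second, the answer in Data Measurements creates a conflict of roles. The coaches help set each man's goals and follow his progress. The curriculum includes a 7% weight-loss target for men above a BMI of 25, weekly weight checks and periodic blood pressure checks. By Week 24 a coach is likely to know which way a man's values have been moving and to hope for improvement.

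The outcomes concerned are the LS7 changes, which are secondary outcomes and which the protocol treats as its measure of effectiveness. Several LS7 metrics are defined by cut-points, such as 120/80 mmHg for ideal blood pressure and 200 mg/dl for ideal cholesterol. Where results are reported by category, a small shift near a boundary can change a man's classification.

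**Working it through.** No arithmetic applies to the size of this problem. The protocol states no standard deviation of change, makes no power calculation and gives no information on recording error. The check is a comparison of the text.

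**1. Who handles the biometric data**

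| Section | Role named | Task |
|---|---|---|
| Data Measurements | Health coaches | Enter the four biometric values |
| Data Management | Study staff | Collect data |
| Data Management | Study team members | Collect data from participants |
| Section E, data accuracy | Coordinator and/or investigator | Responsible for collecting and recording |
| Confidentiality | PI, co-investigators, research assistants | Sole access to data |

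**2. Are coaches simply study staff under another name?** Research Structure has them assisting the study team, and Instructors draws them from student volunteer groups. The more natural reading is that they are a separate group, so the rows above do not reconcile themselves.

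**3. Do the same people deliver and enter?** Yes. The Intervention section and Data Measurements both name the health coaches.

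**4. Who takes the readings?** The protocol does not say. Data Measurements speaks of entry only. The descriptions of the cuff, the finger stick and the waist tape name no operator. Waist circumference is not among the values that coaches enter.

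**5. Could the design absorb a recording shift?** All participants receive the intervention, and the Randomization section says that the earlier walk data are not a true comparison group. If recorded change = true change + shift, the shift passes whole into the estimated time effect. A larger sample would narrow the interval around the shifted value and would not remove the shift. The analysis section mentions between-group contrasts, but with one arm there is no second group to supply one.

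**6. What limits the shift?** Blood pressure comes from an automated device, and cholesterol and glucose from finger-stick assays. Section E promises operating procedures for data collection, REDCap training, and a random audit by the PI of 10% of subjects (10% × 100 = 10 men if enrolment is met). Data Management provides for verification before lock. These act mainly on reading and transcription errors. The protocol states no rule on how many readings are taken or which one is kept, and an audit against source need not show that a reading was repeated or chosen.

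**7. Is another recorder within reach?** A research team member is already required at all testing. Table 1 puts labs and vitals at Weeks 1, 12 and 24, so with 10 teams the requirement is 10 × 3 = 30 team sessions.

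**The case against.** The strongest reply is that this is a matter of delegation. Data Management lets access and entry permissions be set for each individual. Section E can be read as assigning accountability, with keying delegated. Confidentiality can be read as referring to stored data. This stands in part: coach entry is technically possible and may be what was intended. But the word *only* in Confidentiality still excludes coaches, and nothing in the protocol states the delegation.

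A reader might infer that coaches take the measurements and so can repeat, select or round readings. The documents do not support that. They assign entry to the coaches and leave measurement unassigned. Nor do they say how weight and height are read; a manual method is described only for the waist.

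A reader might also want to state how often a recording shift of a few mmHg would produce a significant result. Both the shift and the variability would have to be assumed. Such a figure would show sensitivity to an assumption and would not be evidence that coach entry causes a shift.

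It can be said that the required research team member is there for safety, and that the protocol does not say this person is free to record or independent of coaching. That is correct, so recording would be an added duty. Finally, coordinators and investigators are also unblinded and also have an interest in a good result. That stands too: changing the recorder does not blind anyone. It does remove the overlap between coaching a man and entering his outcomes.

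**Conclusion.** The point holds as an internal contradiction combined with an avoidable role conflict. Data Measurements assigns entry of the four biometric values to the people who deliver the intervention. Data Management, section E and Confidentiality point to research staff.

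The resulting risk is a favourable recording shift in the secondary LS7 changes. Its size is unknown, the existing safeguards limit it in part, and nothing in the protocol shows that it will occur. The primary outcomes, feasibility and acceptability, rest on procedure logs, surveys and qualitative data and are not affected. Severity is low.

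The conclusion assumes that coaches are distinct from the study staff named elsewhere, which the text favours but does not state outright. If coaches were formally part of the study team, the contradiction would shrink and the role conflict would remain.

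**What to change.** Replace the clause in Data Measurements with wording such as: *At Weeks 1, 12 and 24, blood pressure, cholesterol, glucose and body mass will be recorded and entered by the coordinator or a research assistant who does not coach the participant's team.* State in the same place who takes the readings.

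Let coaches keep the interim weight and blood pressure checks, with those values flagged by source so that they are not mixed with the outcome measurements. If coaches enter the interim values in REDCap, say so in Confidentiality and limit their permission to that form. Then use the same role names in Data Measurements, Data Management, Confidentiality and section E.

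The cost is protocol wording, an added recording duty for a research team member, and scheduling a suitable person for the 30 team sessions. The protocol already requires a research team member at testing, so no new post is implied. The change lessens the role conflict and should not be described as blinded assessment. It is best made before the Week 1 measurements.

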### **Outcome Measures:**

#### Primary Outcomes:

- Feasibility and Acceptability

#### Secondary Outcomes (Pre-Post):

## Research Protocol: Creating Healthier Communities – AAMWI & OSU

- Prevalence of participants with a primary care provider
  - Change in social and patient activation needs
  - Change in cardiovascular health as per American Heart Association LS7 Metrics including blood pressure, cholesterol, glucose, smoking, body mass index, physical activity and dietary intake
  - Prevalence of participants participating in OSU ResearchMatch.
- i. We will measure feasibility via the study procedure logs (i.e., study enrollment and study contact completion).

We will assess protocol acceptability (satisfaction, usefulness, and plans and change of behavior to apply health promotion strategies). At the end of each program session, participants will complete a process evaluation via exit survey reviewed by stakeholders. We will use open-ended items to evaluate each participant's SMART goals and progress toward those goals. We will also inquire about what and how the participants like, dislike, and recommend intervention improvement. Specific questions will be: 1) What are your SMART Goals this week? 2) Do you have concerns about your ability to meet the goal(s) you set? If so, list your concern(s). 3) Have you changed your behavior as a result of the intervention? If so, how? 4) On a scale of 0 to 10 (with 0 being not at all satisfied and 10 being completely satisfied) how satisfied are you with this session? 5) On a scale of 0 to 10 (with 0 being not at all useful and 10 being most useful), how useful do you find this session? 6) What was the most useful part of this session? 7) Do you have any additional comments or suggestions?

- ii. Validated Questionnaires will be assessed prior to intervention, 12 weeks (mid-point) and post intervention (24 weeks)
- Centers for Medicare and Medicaid Services Accountable Health Communities Health-Related Social Needs Screening Tool - The Centers for Medicare & Medicaid Services (CMS) Accountable Health Communities Model, tested by the Center for Medicare and Medicaid Innovation, addresses the critical gap between clinical care and community services in the current health care delivery system by testing whether systematically identifying and addressing the health-related social needs of Medicare and Medicaid beneficiaries impacts their total health care costs and improves health. The questionnaire includes 26 questions addressing living situation, food security, transportation, utilities, safety, financial strain, employment, family and community support, education, physical activity, substance abuse, mental health and disabilities.
  - Insignia Health Patient Activation Measure - The Patient Activation Measure (PAM) contains 13 items, segmenting individuals into one of four activation levels along an empirically derived 100-point scale. The four activation levels are 1) disengaged and overwhelmed, 2) becoming aware, but still struggling; 3) taking action and 4) maintaining behaviors and pushing further. Each level provides insight into an extensive array of health-related characteristics, including attitudes, motivators, and behaviors. Individuals in the lowest activation level do not yet understand the importance of their role in managing their own health, and

## Research Protocol:

### Creating Healthier Communities – AAMWI & OSU

have significant knowledge gaps and limited self-management skills. Individuals in the highest activation level are proactive with their health, have developed strong self-management skills, and are resilient in times of stress or change. Each point increase in PAM score correlates to a 2% decrease in hospitalization and 2% increase in medication adherence. The questionnaire has acceptable reliability with  $\alpha=0.80$ .

- Diet History Questionnaire III - The Diet History Questionnaire (DHQ) is a freely available food frequency questionnaire (FFQ) for use with adults. The most recent version, DHQ III, can be used by researchers, clinicians, or educators to assess food and dietary supplement intakes. **It is available as a web-based tool only. Paper and pencil administration is not supported.** The nutrient and food group database for DHQ III is based on a compilation of national 24-hour dietary recall data from the National Health and Nutrition Examination Surveys (NHANES) conducted in 2007-08, 2009-10, 2011-12, and 2013-14 among those 19 years or older. Use in younger age groups is not appropriate given that the food list and portions are based on adult data. DHQ III is available as a web-based tool. DHQ III consists of 135 food and beverage line items and 26 dietary supplement questions. Some line items for foods and beverages have additional embedded questions that allow for final assignment to items in the nutrient and food group database leading to 263 foods/beverages listed in the database. <https://epi.grants.cancer.gov/dhq3/> Prior research has shown that questionnaire is valid and reliable.
- Center for Epidemiologic Studies Depression Scale (CES-D): The CES-D scale is a brief self-report scale designed to measure self-reported symptoms associated with depression experienced in the past week. The items of the scale are symptoms associated with depression which have been used in previously validated longer scales. The CES-D has been shown to be a reliable measure for assessing the number, types, and duration of depressive symptoms across racial, gender, and age categories. High internal consistency has been reported with Cronbach's alpha coefficients ranging from .85 to .90 across studies.
- International Physical Activity Questionnaire -Short Form (IPAQ-SF): Physical activity will be measured using the International Physical Activity Questionnaire. The IPAQ is a 7-item questionnaire designed for adults ages 18-65, assessing time spent walking, in vigorous- and moderate- intensity activity and in sedentary activity in the past week. This measure has shown acceptable test-retest and criterion validity.
- General Ethnic Discrimination Scale: The General Ethnic Discrimination Scale is an 18-item measure of perceived ethnic discrimination that can be used in health research with any ethnic group. The measure assesses both the frequency and the appraisal of discriminatory events in a manner that permits evaluation of the independent contribution of each to health and health behavior. The scale shows high reliability across racial/ethnic groups  $\alpha\sim0.94$ .

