### II. Background and Rationale

In 2010, the American Heart Association (AHA) published 2020 impact goals for cardiovascular health promotion with the aim of improving cardiovascular health and reducing deaths from cardiovascular disease (CVD) and stroke by 20% by the year 2020, which we have modified as shown in Figure 1 for use in the African American Male Wellness Initiative (AAMWI) walk.

| Goal/Metric       |         | Poor health                 | Intermediate health                              | Ideal health                |
|-------------------|---------|-----------------------------|--------------------------------------------------|-----------------------------|
| Current smoking   |         | Yes                         | --                                               | None                        |
| Total cholesterol |         | ≥ 240 mg/dl                 | 200-239 mg/dl or treated to goal                 | <200 mg/dl                  |
| Blood pressure    |         | SBP ≥140 or DBP ≥90 mmHg    | SBP 120-139 or DBP 80-89 mmHg or treated to goal | <120/<80 mmHg               |
| Body mass index   |         | ≥30 kg/m        | 25-29.9 kg/m                         | <25 kg/m        |
| Physical activity |         | Exercise < 3 times per week | --                                               | Exercise ≥ 3 times per week |
| Healthy diet      |         | --                          | --                                               | --                          |
| Glucose           | Fasting | ≥126 mg/dl                  | 100-125 mg/dl or treated to goal                 | <100 mg/dl                  |
|                   | Random  | ≥200 mg/dl                  | 140-199 mg/dl                                    | < 140 mg/dl                 |

Figure 1. Life's Simple 7 Goals for Cardiovascular Health (adapted for AAMWI)

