|-------|----------------------------------------------------------------------------------------------------------------------------------------------------------------------------------------------------------------------------------------------------------------------------------------------------------------------------------------------------------------------------------------------------------------------------------------------------------------------------------------------------------------------------------------------------------------------------------------------------------------------------------------------------------------------------------------------------------------------|----------------------------|------------------------------------------------------------------------------------------|
| 1     | 
 
• Introduction to Life Simple 7 and review of data on Life Simple 7 from the annual AAMWI walk (15 min)
 
• Overview of plan for and goals of the program (15 min)
 
• Purpose: Why did you join the program? What do I hope to achieve? How will healthy eating, physical activity, smoking cessation, blood pressure control, blood sugar control, blood pressure control, weight loss, help myself and others? (20 min)
 
• AHA Check, Change, Control, BP Check Principles (20 min)
 
• How to keep track? Electronic vs. Paper (10 min)
 
• Physical activity assessment, instruction and plan development (10 min)
 
 | American Heart Association | Complete Surveys online via redcap portal prior to Week 1, Labs and Vitals Week 1 |
| 2     | 
 
• Life's Simple 7- Physical Activity (15 min)
 
• DPP Session 5: Move Those Muscles (10 min)
 
• DPP Session 6: Being Active A Way of Life (20 min)
 
• Physical activity assessment, instruction and plan development (30 min)
 
                                                                                                                                                                                                                                                                                                                                                                                                        |                            | Weight Check                                                                             |

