| 12                                                                   | 
 
• DPP Session 9: Problem Solving (15 min)
 
• DPP Session 10: Four Keys to Healthy Eating Out (15 min)
 
• Physical Activity (45 min)
 
                                                                                                                              |                                                                                                                                               | Complete Surveys online via redcap Labs and Vitals |
| 13                                                                   | 
 
• DPP Session 11: Talk Back to Negative Thoughts (30 min)
 
• AHA Check, Change, Control, BP Check
 
• Physical Activity (45 min)
 
                                                                                                                           |                                                                                                                                               | Weight, BP check                                          |
| 14                                                                   | 
 
• DPP Session 12: The Slippery Slope of Lifestyle Change (30 min)
 
• Physical Activity (45 min)
 
                                                                                                                                                                          |                                                                                                                                               | Weight Check                                              |
| 15                                                                   | 
 
• Introduction to Clinical Trials (20 min)
 
• Community Scientist Academy program (10 min)
 
• Physical Activity (45 min)
 
                                                                                                                                         | OSU Center for Clinical and Translational Science                                                                                             | Weight Check                                              |

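### The past-week IPAQ takes in a programme exercise session at Weeks 12 and 24 but not at baseline, so change in activity cannot be read as maintained behaviour unless session exercise is recorded separately

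*Protocol*

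**What the plan says.** Under Outcome Measures, physical activity is one of the Life's Simple 7 (LS7) secondary outcomes. Item ii names the instrument: "Physical activity will be measured using the International Physical Activity Questionnaire". It describes the short form as "assessing time spent walking, in vigorous- and moderate- intensity activity and in sedentary activity in the past week".

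The timing in the same item is "Validated Questionnaires will be assessed prior to intervention, 12 weeks (mid-point) and post intervention (24 weeks". Table 1 is more specific. The Week 1 row reads "Complete Surveys online via redcap portal prior to Week 1, Labs and Vitals Week 1", and the Week 12 and Week 24 rows both read "Complete Surveys online via redcap Labs and Vitals". The Intervention section states "Health coaches will meet with participant teams weekly for 75 minutes". The Week 12 entry includes "Physical Activity (45 min"; Weeks 11, 23 and 24 also list 45 minutes.

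Figure 1 in Background and Rationale gives activity two levels only: ideal is "Exercise ≥ 3 times per week", anything less is poor, and there is no intermediate level.

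Data Measurements assigns the LS7 measures, taken before, midway and after, to the effectiveness and maintenance parts of RE-AIM. The Randomization section confirms a single arm. The Protocol neither separates session exercise from other exercise nor schedules an IPAQ after the sessions have ended.

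**The concern.** The baseline and follow-up questionnaires ask the same question about different kinds of week. Before the programme starts, the recalled week can hold only the man's own activity. At Weeks 12 and 24 it normally also holds a supervised block that the study itself provides. Part of any rise may therefore record that he came to the session.

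Attendance is already counted under the primary feasibility outcome, through adherence. If it also shows up as improved activity, the same fact is credited twice. With no comparison arm, nothing else in the design separates the two. The Week 24 measurement is called post-intervention but falls in the week of the last session, so it does not show what men do once the sessions stop.

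**Working it through.** The Protocol states no effect size or power for this outcome, so there is no figure to reproduce. The check has three steps.

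**1. Recall window against the calendar.** The window is 7 days and sessions are weekly.

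- Baseline, before Week 1: no programme session in the window.
- Week 12: a survey answered after that week's session captures it; one answered before captures the Week 11 session. Both have 45 minutes of activity.
- Week 24: the same holds for the Week 24 and Week 23 sessions, again 45 minutes each.

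The result for a weekly attender does not depend on the day the survey is answered. The contribution is up to 1 × 45 = 45 minutes per week at each follow-up and 0 at baseline. It is 45 if the session is additional to his own exercise, and 0 if it replaces an equal amount.

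**2. Effect on the Figure 1 category.** This assumes that IPAQ answers are converted to times per week and that a session counts as one occasion. The Protocol states neither.

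| Own exercise per week, unchanged | Baseline category | With one session | Follow-up category |
|---|---|---|---|
| 0 | poor | 1 | poor |
| 1 | poor | 2 | poor |
| 2 | poor | 3 | ideal |
| 3 | ideal | 4 | ideal |

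Only men at exactly 2 change category through attendance alone.

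**3. Possible size.** Let q be the share of men at exactly 2 per week and a the share attending in the recall window. The rise in ideal activity, with no change outside the programme and no substitution, is q × a. The Protocol gives neither q nor a, so both are assumed: q from 5% to 30%, a from 50% to 100%. Enrolment of 100 and the expected 10% attrition give 100 × (1 − 0.10) = 90 completers.

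- Low end: 0.05 × 0.50 = 2.5 percentage points, 90 × 0.025 = 2.25 men.
- Between: 0.10 × 0.75 = 7.5 points, 6.75 men; 0.20 × 0.75 = 15 points, 13.5 men.
- High end: 0.30 × 1.00 = 30 points, 27 men.

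For scale, suppose m men switch to ideal and none switch back. The exact two-sided McNemar p-value is 2 × 0.5^m: 0.063 for m = 5 and 0.031 for m = 6. Six men are 6/90 = 6.7% of completers. This is an illustration only, since the Protocol plans mixed-effects linear models, not this test.

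**The case against.** The strongest reply is that nothing is being mismeasured. Group exercise is a core part of the intervention, the stated outcome is change in activity and not activity outside sessions, and a man who exercised for 45 minutes in a session did exercise. Weight, blood pressure and glucose also reflect session exercise, and nobody would subtract it there. This stands: total activity during the programme is a proper outcome. It does not answer the maintenance label, which needs evidence about activity that does not depend on the session.

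Several stronger readings are tempting and are not supported:

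- **Attendance alone makes men ideal.** Step 2 shows that this applies only at exactly two times a week, and only under a conversion that the Protocol does not state. IPAQ scoring is commonly left to the SAP, which was not available here.
- **The shift can be given a narrow range.** Assuming Poisson exercise frequency with mean 1.5–2.5 and 60–90% attendance gives about 15–24 points. Those inputs are not in the Protocol, and the sample is selected for fewer than four ideal metrics, which that model ignores.
- **The distortion always favours the programme.** A man who swaps one of his own workouts for the session gains nothing.
- **Outside-session activity should replace the total.** A man at three times a week who moves one workout into the session would fall to two and be scored poor, although he exercises as much as before.

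It is also fair to say that contact completion is already logged and adherence summarised, so much of the information may exist. What is missing is a stated link between that log and each survey's 7-day window.

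**Conclusion.** The concern holds in a limited form. For regular attenders, the follow-up windows normally contain one programme session and the baseline window none. On the time scale this is worth up to 45 minutes a week, less any substitution, and needs no assumption about categories. On the poor/ideal scale it affects only men at exactly two times a week, and the 2.5 to 30 points shown above rest wholly on assumed shares and attendance.

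The activity outcome is valid as total activity during the programme. A reader might infer that it is biased or that the Protocol has chosen the wrong outcome; the text does not support that. What the design cannot support, with one arm and no IPAQ after the last session, is reading the change as adopted or maintained behaviour. This concerns one of seven LS7 components, a secondary outcome in a pilot without power calculations. It is a cheap improvement to make, and it does not threaten the primary aim.

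**What to change.** - At Weeks 12 and 24, record how many programme sessions the man attended in the past 7 days, by one added survey item or by linking the contact log to the date of each survey.
- Keep total activity as the stated LS7 outcome and report activity excluding programme sessions beside it. State the deduction rule in advance: a session count does not show whether the man reported the block as walking, moderate or vigorous activity. The sessions in these windows are each 45 minutes in Table 1.
- Add a sentence that the total will not be interpreted as adopted or maintained behaviour unless the outside-session result agrees.

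The cost is one survey item or a data link, plus a few sentences in the Protocol. The reported improvement may look smaller. The outside-session figure will understate change for men who substitute the session for their own exercise, which is why it belongs beside the total and not in its place.
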